## Sample size {14}

A sample size of 38 participants (approx. 19 per group) was estimated for this study. The sample size estimation was based on systematic reviews investigating the effects of motor-cognitive training and exergames on cognitive functions. Stanmore et al. included studies with any population (including five out of seventeen studies with stroke or other neurological patients) and found a small to medium effect for global cognitive functioning (SMD = 0.44, *p* = 0.001) and several small to large effects for cognitive domains including executive functions, processing speed and visuospatial skills (0.26 ≤ SMD ≤ 0.90, *p* < 0.05) (132). Five further reviews included studies with older adults and found small to large effect sizes for global or overall cognitive functioning and cognitive domains including attention, executive functions, learning and memory, and processing speed (0.30 ≤ SMD ≤ 1.37, *p* < 0.05) [31, 35, 54, 56, 134]. Based on this evidence, a small to medium effect on global cognitive functioning is anticipated for the planned study (*f* = 0.21). The sample size was estimated using G*Power, entering this effect size (requiring no expected difference between groups and standard deviations) and the following parameters into the mask for a two-way mixed ANOVA; α-level = 0.05, power = 0.80, number of groups = 2, number of measurements = 3, correlation among rep measures = 0.5, nonsphericity correction = 1. Dropouts will be replaced by post-recruitment until the planned sample size is achieved. Based on the recent feasibility study [85] and comparable literature [135–137], a dropout rate of 10–20% can be expected.

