Assumptions on the residuals of primary and secondary outcomes will be checked using the DHARMa package in R [147]. Appropriate actions will be taken if one or more assumptions are not met. All primary and secondary outcomes will be analysed following the standard intention-to-treat (ITT [148, 149]) principle using linear mixed-effects models (LMEM, lme4 package in R). Subject-specific random intercepts will account for within-subject correlations between time points. Follow-up scores (T2) of the outcomes will be the dependent variables of the models, while group (intervention vs. control, control being the reference), time (T0, T1, T2), and group x time interactions at T1 and at T2, respectively, will be included as independent variables (fixed effects). Baseline factors such as age, sex, and time since stroke will be considered as covariates. Missing data of whole measurement time points (i.e. of dropouts) will be accounted for with the ‘last observation carried forward’ method. For single missing data points (e.g. if a participant did not perform an assessment at one time point or a technical issue produced missing data at one time point), however, no data imputation will be performed as LMEMs can be fitted even if some outcome data are missing [145, 150]. For the outdoor walking assessment (OWA), high occurrence of missing data is expected, as ability to walk 400 m is not covered by the eligibility criteria and varying weather conditions on the measurement days may interfere with the assessment. Therefore, for the OWA outcome parameters, datasets of participants who did not perform the OWA at one or several time points will be excluded from the analysis. Significance will be set to *p* < 0.05. Effect sizes will be calculated as *r* (Bravais-Person correlation coefficient) and interpreted as small (*r* < 0.3), medium (*r* < 0.5), and large (*r* ≥ 0.5) [145].

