## Trial status

The protocol version 2 of this study was approved by the local Ethics Committee in Switzerland (Ethics Committee of the Canton Zurich, project-ID: 2022–01211) in August 2022. Since then, three amendments were submitted to the ethics committee: (1) protocol version 3 (October 2022) enclosed a change in the patient information regarding travelling costs to study centres, (2) protocol version 4 (March 2023) reported a new principal investigator at one of the study sites, and (3) protocol version 5 (October 2023) included a more detailed description of the data management, which was suggested by the monitor. None of the amendments changed any of the study procedures. The current version 5 of the protocol was approved by the Ethics Committee on October 20, 2023. Study procedures began in September 2022 and are expected to be completed by July 2024. At the time point of submission of this manuscript, the study is running. At submission of this manuscript, 37 participants were enrolled and planned to completed the study or had already completed it. Nine additional participants had been enrolled but withdrew before study completion. The study was registered on https://clinicaltrials.gov (NCT05524727) on September 1, 2022, as well as on https://.kofam.ch, the portal for human research in Switzerland, which ensures that none of the study procedures have been changed since the start of the study.

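### Dropouts' missed visits are filled by last observation carried forward, although the plan itself says the mixed model needs no imputation; this distorts the effect estimate more than the test

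*Protocol article*

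**What the plan says.** The section on statistical methods for primary and secondary outcomes {20a} sets two rules for missing outcomes.

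- For dropouts: "Missing data of whole measurement time points (i.e. of dropouts) will be accounted for with the" last-observation-carried-forward method.
- For a single missing value, such as one test not done at one visit: "no data imputation will be performed as LMEMs can be fitted even if some outcome data are missing".

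The analysis is described as "following the standard intention-to-treat (ITT [148, 149]) principle using linear mixed-effects models (LMEM, lme4 package in R"), and "Subject-specific random intercepts will account for within-subject correlations between time points". The dropout rule therefore applies to the primary outcome (MoCA total score) and to the secondary outcomes. The exception is the outdoor walking assessment, which has its own exclusion rule.

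On the extent of dropout, the sample size section says that "a dropout rate of 10–20% can be expected" and that "Dropouts will be replaced by post-recruitment until the planned sample size is achieved". The trial status section counts 37 participants who had finished or were expected to finish, and adds: "Nine additional participants had been enrolled but withdrew before study completion".

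**The concern.** The two rules do not fit together. A random-intercept model uses whatever T0, T1 and T2 scores a participant has. It makes no difference to the model whether a missing T1 MoCA comes from a missed test or from a participant who left. The article gives no reason for imputing one and not the other.

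LOCF also touches the trial's stated objectives directly. For someone who leaves before T1, the baseline MoCA is copied to T1 and T2, so change is zero by construction. For someone who leaves after T1, the T1 score is copied to T2. The persistent effect at follow-up, which is a secondary objective, is then partly assumed rather than observed. The section on additional analyses compares the between-group difference in change with a clinically relevant 1.22 MoCA points for outcomes that reach significance, so a shift in the estimate affects interpretation.

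**Working it through.** **The plan's own figures.** The sample size of 38 reproduces. With f = 0.21, 3 measurements, 2 groups and correlation 0.5, the noncentrality is 0.21² × 38 × 3 / (1 − 0.5) = 10.05 on 2 and 72 degrees of freedom. Power is 0.8003 at N = 38 and 0.788 at N = 37. The missing-data rule does not enter that calculation. The withdrawn share is 9 / (37 + 9) = 19.6%, at the top of the expected 10–20%.

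**Assumptions, not in the documents.** 46 randomised 1:1; MoCA SD 3; correlation 0.5; 20% dropout with 70% of it before T1 unless stated; missing at random, so that dropouts would have had the same effect as the others. The assumed effect is 0.44 × 3 = 1.32 points, using the standardised difference for global cognition quoted in the sample size section.

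**Expected LOCF estimate.** After filling, every participant has three scores, and the group × time term equals the difference between arms in mean change from T0. Let p be the share leaving before T1, q the share leaving after T1, δ1 and δ2 the true effects, and g a retest gain common to both arms.

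- With equal dropout: T1 estimate = (1 − p)δ1; T2 estimate = (1 − p − q)δ2 + qδ1.
- With no effect and unequal dropout: T1 estimate = (p_control − p_intervention)g.

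**Scenarios.**

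1. *Effect 1.32 at T1 and T2.* p = 0.20 × 0.70 = 0.14 and q = 0.06. T1: 0.86 × 1.32 = 1.14. T2: 0.80 × 1.32 + 0.06 × 1.32 = 1.14. Simulations gave 1.11 to 1.14 at T1 under LOCF, and 1.30 to 1.33 from the same model on observed data.
2. *Effect 1.32 at T1 but 0 at T2, half of dropouts leaving after T1.* T2: 0.10 × 1.32 = +0.13. Simulations gave +0.12 to +0.17.
3. *No effect, 1-point retest gain, 30% dropout in the intervention arm and 10% in control.* p = 0.21 and 0.07, so T1: (0.07 − 0.21) × 1 = −0.14. Simulations gave −0.13 to −0.18.
4. *Extreme case: all nine withdrawals before T1 and in the intervention arm, no effect, common trend of 0.5 SD.* Bias = 9/23 × 0.5 = 0.20 SD against the direction of the trend. Simulation gave 0.19 SD and type I error of 11–13%, against about 5–6% on observed data.

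**Standard error and test, scenario 1.** The model SE under LOCF was 0.81 and the actual sampling SD of the LOCF estimate was 0.81 to 0.85. The observed-data SE was 0.94. With no dropout it would be 3 × √(2/23) = 0.88. The ratio of estimate to SE was 1.11/0.81 = 1.37 under LOCF and 1.31/0.94 = 1.39 on observed data; power was 0.27 and 0.28. With equal dropout and no effect, type I error under LOCF was 0.05 to 0.06 across runs.

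**The case against.** Several counter-arguments have force.

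- **The count.** A reader might infer that one in five ITT participants will carry invented values. The documents do not support that. The trial status section speaks of enrolment, and the participant timeline places consent and baseline before randomisation, so some of the nine may never have been randomised. Anyone who left after T1 has a genuine T1 score. Nine of 46 is therefore an upper bound for the withdrawals known at submission.
- **The target of estimation.** The attenuation in scenario 1 supposes that dropouts would have had the full effect. If those who left before T1 gained nothing, the ITT effect would itself be 0.86 × 1.32 = 1.14, and the observed-data model at 1.31 would be about 15% too large. The documents settle neither assumption. This stands, and it is why the assumption should be stated and tested.
- **Standard errors and false positives.** It is tempting to say that copied values make the standard error wrong and inflate type I error. The LOCF standard error nearly matches the spread of its own estimate. It is only somewhat smaller than the complete-data value. Clear inflation appeared only in the extreme one-arm scenario; with 30% vs 10% dropout, runs gave 0.053 to 0.066.
- **Partial cover.** The per-protocol analysis drops those who withdrew between T0 and T1, and so removes early carried-forward values. It is a selected set and does nothing about withdrawals after T1.

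None of this supplies a reason for imputing dropouts while leaving single missing values to the model.

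**Conclusion.** The concern holds as a defect in how the effect is estimated. The plan fixes LOCF for dropouts in its main analysis, against the logic of its own next sentence. Up to 19.6% of those enrolled may be affected. Under missing at random with the assumed dropout, a 1.32-point effect is reported as about 1.1. That moves it from above to below the 1.22-point benchmark, while the test result is nearly unchanged. Spurious T2 persistence of about 0.1 to 0.2 point, or a false difference of about −0.13 to −0.18 point, needs the specific effect, dropout and retest assumptions of scenarios 2 and 3. Because the arm and timing of withdrawals are not given, the size and direction of bias in this trial cannot be determined. Nor is LOCF a safe conservative choice: with unequal dropout its bias follows the time trend and can go either way.

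**What to change.** Delete the LOCF sentence. Fit the planned random-intercept model by REML to all observed T0, T1 and T2 scores of every randomised participant, including those who withdrew and were replaced. State that this rests on missing at random. Add one sensitivity analysis for departures from it: either a delta-adjusted analysis or reference-based (control-based) imputation. These are different methods, and one should be named in advance. Report withdrawals by arm and by timing relative to randomisation and T1.

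The change needs no new data and leaves the sample size calculation as it is. In scenario 1 the standard error rises from 0.81 to 0.94, so the interval is about 16% wider (0.94/0.81 = 1.16). Participants with only a T0 score add little information on change, so the analysis depends on the missing-at-random assumption, which the sensitivity analysis is there to probe.

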## Outcomes {12}

Primary and secondary outcomes are collected at three time points (T0–week 0, T1–week 12, T2–week 24; see Table 2, Figs. 1 and 3) by cognitive and motor assessments as well as a health-related-quality-of-life questionnaire. At the baseline measurement (T0), participant characteristics and baseline factors are recorded. Intervention and activity outcomes are collected during the intervention (T0–T1) and the follow-up (T1–T2) periods, respectively. All variables will be aggregated as means or medians, depending on the distribution of the data, and the analysis metric for all will be final values (see the ‘ Statistical methods’ section). An overview of all outcome variables is presented in Tables 3 and 4.

**Table 2 Tab2:** Overview over outcome recording. *ADH*, adherence; *BBS*, Berg Balance Scale; *BQ*, baseline questionnaire, incl. see the ‘ Baseline factors’ section; *TUG(-Cogn)*, (cognitive dual-task) Timed Up and Go test; *CPL*, compliance; *FAC*, Functional Ambulation Category; *FM-LE*, lower-extremity component of Fugl-Meyer assessment; *MoCA*, Montreal Cognitive Assessment; *mRS*, modified Rankin scale; *MRT*, mental rotation test; *NBT*, N-back test; *NIHSS*, National Institute of Health Stroke Scale; *OWA*, outdoor walking assessment; *PCA*, physical and cognitive activities; *PP*, perceived performance; *PTD*, perceived task difficulty; *SIS 3.0*, Stroke Impact Scale; *SRT*, simple reaction test; *Stroop*, Stroop Interference test; *TMT*, Trail Making test; *UC*, usual care; *10MWT*, 10-m walk test

Time (weeks)	0	+ 1–12	+ 12	+ 13–24	+ 24
**Time point**	Baseline (T0)	Intervention period	Post-intervention (T1)	Follow-up period	Follow-up (T2)
**Study staff**	Assessor	Training supervisor	Blinded assessor	Training supervisor	Blinded assessor
**Baseline factors:** BQ, NIHSS, FAC, mRS, BBS, FM-LE	+				
**1° Endpoint:** MoCA	+		+		+
**2° Endpoints:** SIS 3.0, SRT, TMT, Stroop, NBT, MRT, TUG(-Cogn), 10MWT, OWA	+		+		+
**Intervention Endpoints:** CPL, ADH, PTD, PP		+ *(intervention group only)*			
**Activity Endpoints:** UC, PCA		+		+

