Secondary gait outcomes included a 10-m walk test (10MWT) and an outdoor walking assessment (OWA) using inertial gait sensors to analyse temporal and spatial gait parameters.The 10MWT has been found reliable and valid in stroke patients [128]. The 10MWT is performed according to the protocol by Cheng et al. [128], where participants walk 14 m, where only the middle 10 m are timed. The participant starts walking at the 0-m mark, and the stopwatch is started as soon as the first foot crosses the 2-m mark and stopped again when the first foot crosses the 12-m mark, while the participant continues walking to the 14-m mark. At first, a familiarisation trial is performed followed by three trials at comfortable walking and three trials at fast walking speed. Participants are instructed to ‘walk at a comfortable speed’ and ‘walk as fast but safely as possible’, respectively. Participants use their usual walking aid if needed.The OWA is a 400-m walk following an outdoor route without stairs [129]. At each study centre, a suitable route nearby was pre-defined and all participants follow this same route. Participants use their usual walking aid if needed and wear proper footwear for an outdoor walk. They are instructed to ‘walk at a comfortable speed, as if they were on a stroll’. To ensure safety, participants are accompanied by two investigators.

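### One missed outdoor walk removes a participant from all 15 outdoor gait analyses, although the planned mixed model could use the walks that were performed

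*Protocol article*

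**What the plan says.** The Protocol article, Statistical methods for primary and secondary outcomes {20a}, sets a general approach and then an exception for the OWA.

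- General principle: "All primary and secondary outcomes will be analysed following the standard intention-to-treat" principle, with linear mixed-effects models (LMEMs) and a random intercept per participant.
- Single missing assessments, including a test not performed at one visit: "no data imputation will be performed as LMEMs can be fitted even if some outcome data are missing".
- Dropouts who miss whole visits: last observation carried forward (LOCF).
- OWA: "For the outdoor walking assessment (OWA), high occurrence of missing data is expected", because "ability to walk 400 m is not covered by the eligibility criteria and varying weather conditions on the measurement days may interfere with the assessment". The consequence drawn is that "datasets of participants who did not perform the OWA at one or several time points will be excluded from the analysis".

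Under Secondary outcomes, "The OWA is a 400-m walk following an outdoor route without stairs", whereas the inclusion criteria require only a 10 m walk and a Functional Ambulation Category of at least 3. Table 2 lists the OWA as a secondary endpoint at T0, T1 and T2. Table 3 gives it 12 rows; three of them (stance phase, swing phase, swing width) are split by affected and unaffected side, which makes 15 variables.

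**The concern.** A missed outdoor walk is an instance of the situation in which the article says an LMEM needs no special handling. The only ground for treating the OWA differently is that many walks will be missed. Frequent missingness argues against a complete-case rule, because the information thrown away and the scope for selection both grow with it.

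Two things are at stake. The first is precision: someone rained off once loses two usable walks. The second is selection: one of the two named causes, being unable to walk 400 m, is tied to what the OWA measures. The rule removes participants who gain or lose that ability during the trial, and the Discussion expects the training to improve gait and mobility. When the missed walk is at T1 or T2, the analysed set is therefore defined by an event after randomisation.

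**Working it through.** **The article's own figure.** It states no number for the OWA analysis. Its only sample size is 38 (Sample size {14}), with f = 0.21, α = 0.05, power 0.80, 2 groups, 3 measurements, correlation 0.5 and nonsphericity correction 1. For the group-by-time interaction, λ = N·f²·m/(1 − ρ) = 38 × 0.0441 × 3 / 0.5 = 10.05, with 2 and (38 − 2) × 2 = 72 degrees of freedom. This gives power 0.8003; 37 gives 0.788. The figure of 38 reproduces and is the denominator below.

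**Variables.** Speed, cadence, stride length and its variability, stride time and its variability, and double support time (7); stance, swing and swing width on two sides (6); asymmetry index and walk ratio (2). Total 15.

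**What the rule leaves.** The article calls the missingness high but gives no rate, so q, the share of walks missed at each visit, is an assumption. Two extremes bracket the result.

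| q (assumed) | 10% | 20% | 30% |
|---|---|---|---|
| *Misses independent across visits* | | | |
| Complete share, (1 − q)³ | 0.729 | 0.512 | 0.343 |
| Participants kept, of 38 | 27.7 | 19.5 | 13.0 |
| Walks performed, 3 × 38 × (1 − q) | 102.6 | 91.2 | 79.8 |
| Walks analysed, 3 × 38 × (1 − q)³ | 83.1 | 58.4 | 39.1 |
| Performed walks discarded, 1 − (1 − q)² | 19% | 36% | 51% |
| *The same people always miss* | | | |
| Participants kept, 38 × (1 − q) | 34.2 | 30.4 | 26.6 |
| Performed walks discarded | 0% | 0% | 0% |

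As an illustration only, since f = 0.21 was set for global cognition, the same power formula gives 0.66, 0.47 and 0.32 with 28, 19 and 13 participants, and 0.75, 0.69 and 0.64 with 34, 30 and 27.

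**Misses at random, as with weather.** A simulation with 19 per arm, correlation 0.5, a true effect of 0.5 SD at T1 and T2 and 2,000 runs compared complete cases with generalised least squares (known covariance) on all observed walks. For the T0-to-T1 effect, both methods centre on 0.50 to 0.51. The complete-case variance is 1.22, 1.57 and 2.01 times the other at q = 10%, 20% and 30%. The cost is precision, not bias.

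**Misses that depend on observed walking.** In the same set-up, T0 is complete, and walks at T1 and T2 are missed more often by weak baseline walkers in the control arm only. For a true 0.50, complete cases then give 0.66, 0.75 and 0.80; the available-data estimate gives 0.50, 0.51 and 0.51. This mechanism is assumed. It shows what the rule can do, not what it will do here.

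**The case against.** The rule is prespecified, reasoned and clearly worded. A reader might call it a contradiction of the intention-to-treat statement, but the text reads as a general rule followed by an explained exception. It is a weak choice, and nobody is left unsure that it applies to a missed OWA. A reader might also infer that data are deleted; the exclusion covers only the OWA analyses, and those participants' other outcomes stay in.

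A stronger inference is that the randomised comparison is broken. The documents do not support that in general. Participant timeline {13} places T0 before randomisation, so exclusion for a missed T0 walk does not disturb comparability. Weather gaps are plausibly unrelated to gait. Only misses at T1 or T2 linked to walking ability can do harm, and nothing in the article shows that these will differ by arm.

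The alternative also has limits. Someone who never walks 400 m contributes no OWA value to either analysis. If a walk is missed because of current inability that earlier values do not predict, the likelihood model is not valid either. And because inability tends to persist, the true loss may lie nearer the same-people end of the table.

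Finally, the consequences are contained: the secondary objectives are exploratory, and the 10-m walk test gives the same spatiotemporal parameters indoors without this exclusion. All of these points stand. They narrow the concern, but none is a reason to discard walks that were performed.

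**Conclusion.** The point holds as one of efficiency and possible selection. The exclusion departs from the article's intention-to-treat statement and from its available-data rationale, and it discards valid walks of participants who perform the OWA at some visits but not others. For misses at T1 or T2 it conditions on a post-randomisation event that may relate to walking ability; misses at T0 or from weather cost mainly precision.

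The size depends on a rate the article does not give. At an assumed 10% to 30% missed per visit, the analysed set falls to between 28 and 13 of 38 if misses are independent, and to between 34 and 27 if they always fall on the same people. In the second case the rule loses no performed walk. The 15 OWA variables are affected; the primary MoCA analysis and all other outcomes are not.

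**What to change.** Replace the exclusion with a statement that OWA outcomes are analysed with the planned LMEM on every observed OWA visit of all randomised participants. Add that no OWA values are carried forward for dropouts. Removing the exclusion alone would return their missing OWA visits to the LOCF rule, and the article does not say how the two rules interact now.

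Report OWA completion by arm and visit, with the reason missed (weather or inability) where it was recorded. The article records protocol deviations in the eCRF but does not say that this reason is coded for each missed walk.

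State that the model assumes data missing at random, that it recovers nothing for participants who never perform the OWA, and that misses from current inability remain a limitation. The complete-case analysis can be kept as a sensitivity analysis.

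The cost is a few sentences and one descriptive table, with no new measurements.
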